**Methods:**

In this randomized waitlist controlled trial, cancer survivors experiencing anxiety- or cancer-related neuropathy (200 for neuropathy and 200 for anxiety) and who had finished primary cancer treatment were invited to participate. Data were collected at 3 time points regardless of randomization condition: baseline, 8 weeks, and 16 weeks. Both face-to-face and web-based recruitment strategies were used. The trial was opened for 2 separate primary outcomes (anxiety- or cancer-related neuropathy). The goal was not to compare these groups but to compare treatment and waitlist groups for each condition. In addition to evaluating the impact of mobile mindfulness on reported anxiety- or cancer-related neuropathy, other pain, fatigue, trauma, sleep, and satisfaction with the Mindfulness Coach app will also be assessed.

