Mindfulness Coach, an iOS- and Android-based mobile app, is designed to deliver a mobile mindfulness training course designed by researchers from the US Department of Veterans Affairs [21,28]. The senior author of this paper, ER, was part of the team that developed the most recent version of the app. Initially developed among other mobile apps in collaboration with the US Department of Defense [28], Mindfulness Coach is freely available to the general public for both iOS and Android operating systems. A recent study exploring the effects of the app among the general population found that use of the Mindfulness Coach app was feasible, and increased use was strongly correlated with an increase in scores measuring mindfulness characteristics including observing, describing, acting with awareness, nonreactivity to inner experience, and nonjudging of inner experience, as measured by the Five-Facet Mindfulness Questionnaire Short Form (FFMQ-SF) [21,29]. Although mobile health is increasingly being used in research and clinical settings, a recent systematic review and meta-analysis concluded that there is still inconclusive evidence due to small nonsubstantial effects of interventions, as well as concerns regarding study quality [30].

Given the persistent effects of diagnosis and treatment and the limitations of in-person offerings in most places, the Mobile Mindfulness Study was conducted to test the impact on anxiety- and cancer-related neuropathy after 8 weeks of use of the Mindfulness Coach mobile app. The study contains the following secondary aims: evaluate the impact of mobile mindfulness on general pain, fatigue, trauma, and sleep, in addition to evaluating the satisfaction with the Mindfulness Coach mobile app. The goal of this paper is to describe the study design.

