## Methods

### Study Design

The study is being conducted with a randomized waitlist control design, such that participants were randomized through Qualtrics to either begin the intervention immediately or after 8 weeks. In addition, participants were invited to participate with the goal of impacting anxiety- or cancer-related neuropathy as a primary outcome (additional discussion on this below). The goal was to have 200 people complete the 8-week survey measures in each group. Funding was originally garnered to examine anxiety as a primary outcome, with additional seed funding received through the University of Hawai’i Cancer Center to test the same design for cancer-related neuropathy. These groups will not be compared with each other, rather, each treatment group (anxiety- and cancer-related neuropathy, respectively) will be compared with each waitlist control group (anxiety- and cancer-related neuropathy).

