#### Intervention

Mindfulness Coach provides simple written instructions and a brief tutorial that introduces the major features, including a training plan, practice exercises, learning topics, and tracking via the app. Mindfulness exercises are delivered via brief, guided audio mindfulness exercises. This information has been arranged in such an order that it is helpful to have learned the material prior to any given session, although not necessary. The core meditation centers around the seated mindfulness practice, and as the sessions go on, users are asked to sit for longer periods of time, building physical and mental capabilities for meditation. Through this process, participants are instructed to bring nonjudgmental awareness to what they are experiencing in a basic sensorial way (eg, what they are feeling on their skin, hearing in the environment, and experiencing inside their body in regard to physical or emotional sensations or thoughts), with a primary aspect of this involving paying attention to and deepening one’s breathing. The app delivers 14 sessions (levels) that each include a prerecorded guided audio meditation exercise. The app also provides a mindfulness self-assessment tool through the FFMQ-SF [29], which users are reminded, but not required, to complete at levels 1, 7, and 14. Assessment feedback “quick tips” are provided based on the results of the FFMQ-SF.

The intervention includes 8 weeks of Mindfulness Coach. (see Figure 2 for examples of features included in Mindfulness Coach). This practice is encouraged daily through the app and participants are asked to build the amount of time they are spending daily. There are many other audio recordings that are placed throughout the sessions, including meditations around scanning the body for sensations, awareness, and processing of difficult emotions, eating mindfully, and loving kindness. Participants are asked to use Mindfulness Coach for 8 weeks, either immediately (treatment group) or 8 weeks after the baseline assessment (waitlist control group).

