## Results

### Overview

We will conduct the primary evaluation of the intervention, comparing changes in multiple outcomes between the treatment and waitlist control groups. Participants were randomized using a simple, open-label (nonblinded) randomization procedure. The intervention was individually guided and conducted electronically. We will follow an intent-to-treat approach, in which individuals are analyzed based on their randomization groups, regardless of adherence. Adherence effects will be examined in a subsequent analysis.

To account for repeated measures, we will run a mixed (both between- and within-subjects variables) linear or logistic model for each outcome. The independent variables are the randomization group (treatment vs waitlist control), time (baseline, 8 weeks, or 16 weeks), and the group by time interaction. The interaction term tests the intervention effect. For all analyses, the assumptions of the models will be checked and remedial measures (eg, transformations and nonparametric tests) will be taken as needed. Logistic models will assess dichotomous outcomes and linear models will assess continuous outcomes. Potential confounders (adherence, age, sex, and race or ethnicity) will be included. Where possible we will run the analyses within subgroups defined by these covariates, providing information on whether the intervention was more effective in certain groups (moderator effects). If there is evidence of nonrandom missing data, such as by differential dropout between groups, we will apply multiple imputation procedures. SAS (version 9.4; SAS Institute Inc) will be used to perform all analyses.

Data collection began in 2019 and was completed in 2023. We had very differential rates of recruitment for the differing arms with reaching near the target for the anxiety arm yet not for the cancer related neuropathy arm. This, along with other outcomes of the study will be reported in a separate manuscript.

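### The test named for the intervention effect spans week 16, when the waitlist arm has also used the app; only the baseline-to-week-8 contrast compares app with no app

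*Protocol article*

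**What the plan says.** All references are to the protocol article.

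- **Design.** Under Study Design, participants are "randomized through Qualtrics to either begin the intervention immediately or after 8 weeks". The Intervention section adds that each arm is asked to use the app for 8 weeks. The treatment arm's period is therefore weeks 0 to 8 and the waitlist arm's is weeks 8 to 16.
- **Assessments.** The abstract says "Data were collected at 3 time points regardless of randomization condition: baseline, 8 weeks, and 16 weeks".
- **Question.** The end of the Introduction says the study was run to "test the impact on anxiety- and cancer-related neuropathy after 8 weeks of use of the Mindfulness Coach mobile app". Study Design sets the recruitment goal at the same horizon: "The goal was to have 200 people complete the 8-week survey measures in each group".
- **Model and test.** Results, Overview lists as independent variables the randomization group, "time (baseline, 8 weeks, or 16 weeks), and the group by time interaction". It then says: "The interaction term tests the intervention effect".

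The article names no 8-week contrast and gives the week-16 comparison no role of its own. It does not say outright whether time is categorical or linear.

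**The concern.** A waitlist control is untreated only while it waits. At week 8 the arms differ by app versus no app. At week 16 both arms have been offered the full 8 weeks, and they differ only in when: one finished 8 weeks ago, the other has just finished. An interaction over all three times pools these two contrasts into one test.

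At stake is what a significant result would mean. The trial asks about benefit after 8 weeks of use. The declared test can reject because of week 16, and as a 2-df test it has no direction, so its rejection is not by itself evidence on that question. The rule applies to each outcome in both the anxiety and the neuropathy group.

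**Working it through.** **1. Reproduce the plan's own figure.** The Power section gives two-sided alpha .005 (0.05/10), 80% power, 200 per group and a detectable d of 0.37.

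- Detectable d = (z_0.9975 + z_0.80) × √(2/n) = (2.807 + 0.842) × √(2/200) = 0.365.
- For d = 0.37 this needs n = 195 per arm; at 200 per arm power is 0.814 (0.809 with the t distribution).

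The figure reproduces. It is a calculation for one two-group contrast, not for an interaction over three times.

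**2. Set up the two tests.** Let d8 and d16 be the standardized arm differences at weeks 8 and 16, positive when they favour the treatment arm, with no difference at baseline. The following are assumed and are not in the article: compound symmetry with correlation ρ = 0.5, complete data, equal arms, and time categorical for the 2-df test.

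- Week-8 change contrast: variance (2/n) × 2(1 − ρ) = 0.01 × 1 = 0.01, so SE = 0.1. For d8 = 0.37, z = 3.7 and power = Φ(3.7 − 2.807) = 0.814. At ρ = 0.5 this equals the plan's own single-contrast power.
- 2-df interaction: the covariance of the two change differences is V = (2/n)(1 − ρ) × [[2, 1], [1, 2]] = [[0.010, 0.005], [0.005, 0.010]]. The noncentrality is λ = (d8² − d8·d16 + d16²)/0.0075. The critical value is −2 ln(.005) = 10.597.

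**3. Results at 200 per group, alpha .005.**

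| Pattern | d8, d16 | λ | 2-df interaction | Week-8 contrast |
|---|---|---|---|---|
| No effect at either visit | 0, 0 | 0 | 0.005 | 0.005 |
| Difference at week 16 only, waitlist better | 0, −0.37 | 18.25 | 0.875 | 0.005 |
| Waitlist half catches up | 0.37, 0.185 | 13.69 | 0.723 | 0.814 |
| Waitlist fully catches up | 0.37, 0 | 18.25 | 0.875 | 0.814 |

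The second and fourth rows have the same λ. The interaction test alone cannot tell a week-8 benefit that the waitlist arm later matches from no week-8 difference and a later advantage for the waitlist arm.

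**4. Range over ρ = 0.5 / 0.6 / 0.7.**

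- Week 16 only: interaction 0.88 / 0.95 / 0.99, week-8 contrast 0.005 throughout.
- Half catch-up: interaction 0.72 / 0.85 / 0.95, week-8 contrast 0.81 / 0.91 / 0.98.
- Full catch-up: interaction 0.88 / 0.95 / 0.99, week-8 contrast 0.81 / 0.91 / 0.98.

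**5. Sensitivity to size.** The Participants section gives 200 in total per condition, which is 100 per arm if allocation is 1:1. At ρ = 0.5 the pairs (interaction, week-8) become 0.47 and 0.005 (week 16 only), 0.32 and 0.42 (half catch-up), 0.47 and 0.42 (full catch-up). Power is lower but the pattern is the same.

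**6. If time were linear.** With three equally spaced times, the slope difference depends only on the week-16 minus baseline change. Under full catch-up its expectation is zero and rejection equals alpha, 0.005. Under half catch-up z = 0.185/0.1 = 1.85 and power = Φ(1.85 − 2.807) = 0.17.

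**The case against.** The case on the other side has real force.

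- **The test is valid for the null of no effect.** If the app does nothing, both contrasts are zero and the error rate is held. This stands. A reader might take 88% beside 0.5% for a false-positive rate; it is not one, because in that row the arms truly differ at week 16.
- **The week-16-only pattern is a stress case.** It needs delayed use to work differently from immediate use, worsening after stopping, or differential dropout. The article forecasts none of these and mentions differential dropout only as a contingency for imputation. A result in the wrong direction would also show in the estimates. This stands too: the row shows what a rejection can mean, not what is likely.
- **Power need not suffer.** With full catch-up the 2-df test does slightly better than the week-8 contrast. This stands.
- **Linear time is hypothetical.** A reader might infer that a real effect would vanish from the analysis. That requires linear coding, which the article does not state and which its list of three discrete times does not suggest.
- **The 8-week horizon is in the article, and an analysis plan may name the contrast.** This answers the point only in part. The article does not merely leave the contrast out; it says which term is the test. A plan naming the week-8 contrast as primary would have to depart from that statement.

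**Conclusion.** The point holds as one about the target of the test. The declared interaction covers a period without an untreated control, while the stated question concerns 8 weeks of use. That conclusion follows from the design and needs no figures.

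The size, at the plan's 200 per group, alpha .005 and d 0.37, with the assumed ρ of 0.5, compound symmetry and complete data: a difference confined to week 16 is declared an intervention effect 88% of the time, against 0.5% for the week-8 contrast. Power is 72% against 81% with half catch-up and 88% against 81% with full catch-up.

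The documents do not support reading this as inflated type I error, as a general loss of power, or as a real effect disappearing. The first is ruled out when the app has no effect, the second depends on how far the waitlist arm catches up, and the third arises only under a linear time coding that is not stated.

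**What to change.** In the analysis section:

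1. State that time is categorical.
2. Name the treatment-minus-waitlist difference in change from baseline to week 8 as the primary 1-df contrast, taken from the same repeated-measures model.
3. Report week 16 separately, as maintenance in the treatment arm and delayed-start replication in the waitlist arm.
4. Make no app-versus-no-app claim from the week-16 contrast or from the overall interaction.

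The cost is a few sentences and one contrast statement in SAS; no new data are needed. The article reports data collection as complete, so the choice should be documented before arm comparisons are examined. Made afterwards, it would be post hoc.

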### Power

Assuming a Bonferroni corrected (for 10 outcome measures) 2-tailed type I error rate (α) equal to .005 (0.05/10), 80% power, and 200 participants per group (400 total), a standardized difference (Cohen *d* effect size) of 0.37 will be detectable. Cohen *d* is the standardized difference and can be converted to the original units by multiplying the SD of the original variable.

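### Age, sex and race/ethnicity, read naturally as main effects, adjust almost nothing in the group-by-time interaction that tests the intervention

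*Protocol article*

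**What the plan says.** The Overview under Results in the protocol article gives the model in three steps.

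- Terms: "The independent variables are the randomization group (treatment vs waitlist control), time (baseline, 8 weeks, or 16 weeks), and the group by time interaction".
- Test: "The interaction term tests the intervention effect".
- Covariates: "Potential confounders (adherence, age, sex, and race or ethnicity) will be included".

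Baseline is therefore one of the modelled responses, not a predictor. Group by time is the only interaction named for the model. The form in which the covariates enter is not stated.

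The same section plans linear and logistic versions ("Logistic models will assess dichotomous outcomes and linear models will assess continuous outcomes"), separate subgroup analyses ("Where possible we will run the analyses within subgroups defined by these covariates"), and multiple imputation if missingness looks nonrandom. On allocation it says: "Participants were randomized using a simple, open-label (nonblinded) randomization procedure". No stratification is described.

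**The concern.** Calling age, sex and race/ethnicity potential confounders and including them signals that the intervention effect will be adjusted for them. The tested effect, however, is a difference in within-person change. A covariate that does not change over time, entered as a main effect, moves a participant's score by the same amount at every visit and drops out of change.

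Three things are at stake. A chance imbalance in a factor that predicts change would stay in the estimate. Any precision from that factor would be lost. And the report would claim an adjustment that, for the tested term, did not take place. Simple randomisation makes chance imbalance possible. It matters most in the neuropathy condition, which the article says did not come near its recruitment target.

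**Working it through.** **The plan's own figure.** The Power section gives a detectable d of 0.37 at two-sided alpha 0.005, 80% power and 200 per group. Check: (2.807 + 0.842) × √(2/200) = 0.365, so it reproduces. It uses no covariates, and this point leaves it untouched.

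**Algebra.** For participant i with group g, time-constant covariates x and visit t = 0, 1, 2:

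y_it = α + τ_t + γ·g_i + δ_t·g_i + θ·x_i + e_it, with τ_0 = δ_0 = 0.

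The change to 8 weeks is y_i1 − y_i0 = τ_1 + δ_1·g_i + (e_i1 − e_i0). The term θ·x_i is gone. With complete data, the estimate of δ_1 is the difference between arms in mean change, whatever θ is and whatever common covariance is used. If the covariates are crossed with time, the change contains (θ_1 − θ_0)·x_i and the adjustment is real.

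**Numerical check.** Simulated data, 200 people, three visits, one data set per scenario, all parameters assumed. Entries are the 8-week interaction (SE).

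| Scenario | No covariates | Main effects | Covariate × time |
|---|---|---|---|
| Linear, complete, age imbalanced by 0.5 SD, random intercept | −0.31826 (0.11409) | −0.31826 (0.11409) | −0.33757 (0.11561) |
| Same data, unstructured covariance | −0.31826 (0.11219) | −0.31826 (0.11219) | −0.33757 (0.11141) |
| Linear, complete, age affects change, random intercept | −0.02358 (0.12688) | −0.02358 (0.12688) | −0.09092 (0.12608) |
| Linear, about 30% of follow-up missing by age and arm, random intercept | −0.46607 (0.13502) | −0.45376 (0.13447) | −0.41700 (0.13834) |
| Random-intercept logistic, complete | −1.552 (0.534) | −1.540 (0.533) | −1.614 (0.559) |

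With complete linear data, the first two columns agree to five decimals in estimate and SE under both covariance structures. With missing visits the estimate moves by 0.466 − 0.454 = 0.012, about 0.09 of its SE. The random-intercept logistic estimate also moves by 0.012. A logistic GEE moved more, from −0.934 to −1.143, but the article specifies a mixed model.

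**Size of the loss.** Assumptions: 100 per arm (the Participants section gives 200 total per condition; 1:1 allocation is assumed), and a covariate correlating r with change.

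- Variance removable by real adjustment is r²: 0 at r = 0, 0.1² = 1% at r = 0.1, and 0.3² = 9% at r = 0.3.
- The SD of a chance imbalance is √(2/100) = 0.141 covariate SDs, and its mean absolute size is 0.141 × √(2/π) = 0.113. The average shift is r × 0.113, which is 0.011 at r = 0.1 and 0.034 at r = 0.3, in SDs of change.
- In 95 of 100 allocations the shift stays below r × 1.96 × 0.141, which is 0.03 at r = 0.1 and 0.08 at r = 0.3.

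Covariate-by-time terms are not free. In the first row of the table they raised the variance by (0.11561/0.11409)² − 1 = 2.7%.

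**What a baseline-adjusted analysis gains.** With equal variances and baseline-to-8-week correlation ρ, the variance relative to unadjusted change is (1 − ρ²)/[2(1 − ρ)] = (1 + ρ)/2. At an assumed ρ of 0.5 this is 0.75, a 25% cut. Simulations with the covariates also included gave cuts of about 24 to 32%. Most of that comes from the baseline score, not from age, sex or race/ethnicity.

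**The case against.** The strongest reply is that the article never says the covariates enter as main effects only. It is a condensed report, and a fuller plan may cross them with time. That stands as a limit: main effects are inferred. They are still the natural reading, since the article names its terms and the tested term and crosses nothing with time except group. The point is therefore about what the stated specification does, not about a missing detail.

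A reader might also infer any of the following, none of which the documents support.

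- *The adjusted result must equal the unadjusted one throughout the trial.* The identity is exact only for linear models with complete data. The article also plans logistic models and expects that data may be missing. Adherence, in the same list, can vary over time and need not cancel. Its inclusion is a separate problem.
- *The intervention test is confounded.* Under randomisation the unadjusted interaction is unbiased, and comparing changes already removes any constant effect of age, sex or race/ethnicity on level.
- *The distortion is large.* One simulated example moved from 0.400 to 0.302 (truth 0.30) once covariates were crossed with time. It assumed a 0.3 SD imbalance, which at 100 per arm is 0.3/0.141 = 2.1 SDs of chance (about 3% two-sided), and a covariate effect on change of 0.3 per SD. Neither figure is in the article.

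The planned subgroup analyses let time trends differ by these factors, which helps in part, but they give no pooled adjusted estimate.

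**Conclusion.** The concern holds in limited form and is minor. Read naturally, the stated adjustment for age, sex and race/ethnicity leaves the tested interaction unchanged for complete continuous outcomes, and almost unchanged with missing visits or in a random-intercept logistic model. The equality of estimates follows from the algebra. The equality of standard errors was checked for random-intercept and unstructured covariance.

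The validity of the test is not in question. What is lost is some precision and some correction of chance imbalance, of the modest size worked out above. Those sizes rest on assumed correlations and on 100 per arm; at 200 per arm the shifts would be smaller by a factor of √2. The firmer complaint is about description: a result would be reported as adjusted for three factors that did almost nothing to it.

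**What to change.** For continuous outcomes, estimate the 8-week effect by regressing the 8-week score on group, baseline score, age, sex and race/ethnicity, or by the equivalent mixed model with baseline as a covariate. Main effects then do adjust the treatment term. This changes the primary model and how baseline is handled, so it should be chosen openly for that reason too.

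If the present model is kept, state that age, sex and race/ethnicity enter with their interactions with time. If neither is adopted, do not describe the interaction as adjusted for these factors.

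The cost is a sentence or two of analysis wording, a few degrees of freedom, and a slight loss of precision from covariate-by-time terms if the covariates do not predict change. No new data are needed. Data collection is finished, so the choice should be recorded before outcomes are compared by arm.

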#### Participants

Cancer survivors experiencing anxiety- or cancer-related neuropathy who had finished primary treatment for cancer were invited to participate in the study. They were first screened and then consented via Qualtrics, where all data were collected, as well. Inclusion criteria were the same for both groups, aside from the different scales used to measure levels of anxiety or neuropathy. Inclusion criteria for both groups include a previous diagnosis of cancer, other than nonmelanoma skin cancer; completion of primary treatment for cancer; not currently practicing meditation for more than 1 hour per week; age older than 21 years; comfortable reading and writing in English; routine access to the internet; and own a smartphone or tablet. There are no exclusion criteria.

For the anxiety group, participants needed to be experiencing cancer-related anxiety, per self-report, as indicated by a score of 22 or higher on the PROMIS (Patient Reported Outcomes Measurement Information System) anxiety short form measure [32]. For the neuropathy group, participants needed to be experiencing CIPN, per self-report, as indicated by a score of 22 points or higher on the Functional Assessment of Cancer Therapy-Cognitive subscale (FACT-GOG-Ntx) CIPN items [33]. The study was powered to examine differences between groups with 200 people in each group (200 total for anxiety, 200 total for neuropathy).

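### Moderator effects are to be read from separate within-subgroup runs, which do not test whether the app's effect differs between subgroups

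*Protocol article*

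**What the plan says.** All the relevant text is in the protocol article, Results, Overview, with sample sizes from Participants and Power.

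- The model: "The independent variables are the randomization group (treatment vs waitlist control), time (baseline, 8 weeks, or 16 weeks), and the group by time interaction". Its role: "The interaction term tests the intervention effect". This is the only interaction named, and it addresses the overall effect.
- The covariates: "Potential confounders (adherence, age, sex, and race or ethnicity) will be included".
- The moderator method: "Where possible we will run the analyses within subgroups defined by these covariates, providing information on whether the intervention was more effective in certain groups". The sentence ends by calling these moderator effects.
- The error rate and size: "2-tailed type I error rate (α) equal to .005 (0.05/10), 80% power, and 200 participants per group (400 total", from which an "effect size) of 0.37 will be detectable". The division by 10 is for outcome measures; nothing is stated for subgroups.
- The Participants section gives a different size: "200 people in each group (200 total for anxiety, 200 total for neuropathy".

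The Overview also commits to intent-to-treat analysis, defers adherence effects to a later analysis, and reports that the neuropathy recruitment target was not met.

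**The concern.** Whether an intervention works better in one group than in another is a question about the difference between two effects. Fitting the group-by-time model once per stratum answers another question: is the effect in this stratum distinguishable from zero? That answer depends heavily on stratum size. Two strata with the same true effect can easily fall on opposite sides of a significance threshold.

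The method and the purpose are both stated in the article, and they do not match. This is therefore more than a detail left to an analysis plan that is not shown: an interaction term there would replace the stated method. At stake is a published statement that the app helps one age, sex or racial or ethnic group more than another, with no test behind it.

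The covariate list also includes adherence. Use of the app arises after randomisation, and the waitlist arm is not asked to use it before week 8 (Intervention section), so strata on adherence are not randomised comparisons. This is a separate defect, and an interaction term would not cure it.

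**Working it through.** **Inputs from the article.** Two-sided alpha .005, 80% power, d = 0.37 and 200 per arm (Power); 200 in total per condition (Participants).

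**Assumptions.** 1:1 allocation, so 100 per arm per condition (ratio not stated). Two strata, split 50/50 or 30/70 (shares not given). A simple two-arm comparison of means, since no within-person correlation is given. Alpha .05 and d = 0.5 are added as a range.

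**1. The plan's own figure.** d = (z(1−alpha/2) + z(power)) × √(2/n) = (2.807 + 0.842) × √(2/200) = 0.365; the noncentral t gives 0.367. The stated 0.37 is reproduced, but for 200 per arm. With 100 per arm the same formula gives 3.649 × √(2/100) = 0.516 (0.521 by noncentral t).

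**2. Disagreement between strata under a uniform effect.** With p1 and p2 the power in each stratum (noncentral t, same true d in both), the chance that exactly one is significant is p1(1−p2) + p2(1−p1).

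| Per arm | d | alpha | Split | p1 | p2 | Disagreement |
|---|---|---|---|---|---|---|
| 100 | 0.37 | .005 | 50/50 | 0.160 | 0.160 | 27% |
| 100 | 0.37 | .005 | 30/70 | 0.078 | 0.258 | 30% |
| 100 | 0.37 | .05 | 50/50 | 0.449 | 0.449 | 49% |
| 100 | 0.37 | .05 | 30/70 | 0.291 | 0.585 | 54% |
| 100 | 0.5 | .005 | 50/50 | 0.360 | 0.360 | 46% |
| 100 | 0.5 | .005 | 30/70 | 0.175 | 0.543 | 53% |
| 100 | 0.5 | .05 | 50/50 | 0.697 | 0.697 | 42% |
| 100 | 0.5 | .05 | 30/70 | 0.478 | 0.836 | 52% |
| 200 | 0.37 | .005 | 50/50 | 0.414 | 0.414 | 49% |
| 200 | 0.37 | .005 | 30/70 | 0.208 | 0.605 | 56% |
| 200 | 0.37 | .05 | 50/50 | 0.740 | 0.740 | 38% |
| 200 | 0.37 | .05 | 30/70 | 0.520 | 0.870 | 48% |

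Worked example, first row: 2 × 0.160 × 0.840 = 0.269. All rates are for one two-level covariate and one outcome.

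**3. No effect in either stratum.** The rate is 2 × alpha × (1 − alpha): 2 × .005 × .995 = 1.0%, and 2 × .05 × .95 = 9.5%.

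**4. The interaction test.** Its false-positive rate is its nominal alpha (0.5% or 5%) whether or not the app works. The difference in effects detectable with 80% power is (z(1−alpha/2) + z(0.80)) × √(2/n1 + 2/n2), with n1 and n2 per arm in each stratum.

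- 100 per arm, 50/50: √(2/50 + 2/50) = 0.283. At alpha .05, 2.802 × 0.283 = 0.79; at alpha .005, 3.649 × 0.283 = 1.03.
- 100 per arm, 30/70: √(2/30 + 2/70) = 0.309. At alpha .05, 0.86; at alpha .005, 1.13.
- 200 per arm: 0.56 to 0.61 at alpha .05 and 0.73 to 0.80 at alpha .005.

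**The case against.** The strongest objection is that the article states no decision rule. It says that subgroup runs will be done where possible and will be informative. A reader might infer that moderation will be declared whenever one stratum is significant and the other is not. The text does not say this, and showing subgroup estimates with intervals fits it equally well. All of the disagreement rates are therefore conditional on a practice that the article does not state. What remains is that no stated analysis compares the strata.

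A reader might also infer that spurious differences will be common whatever the app does. The figures do not support that. If the app has no effect the rate is 1.0% to 9.5%, and for a small effect (d = 0.2, alpha .005, 50 per arm per stratum) it is 6.6%. At the plan's own alpha and effect size, with 100 per arm, it is 27% to 30%, below the rates at alpha .05.

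The analysis is also secondary. The overall group-by-time comparison and the intent-to-treat commitment are untouched, and nothing here casts doubt on them. Finally, the interaction test is weak at this sample size. That is true and limits what the change can deliver, but low power is no reason to prefer runs that do not address the question.

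**Conclusion.** The concern holds in a limited form. The article's stated way of learning about moderation does not test moderation, and no term that would do so is stated.

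If subgroup significance is compared, and the app has a real effect of d = 0.37 to 0.5 that is the same in both strata, they would disagree in 27% to 54% of trials per covariate and outcome with 100 per arm. With the Power section's 200 per arm and d = 0.37 the range is 38% to 56%. These figures rest on 1:1 allocation, two strata split between 50/50 and 30/70, and a simple comparison of means. Neuropathy strata would be smaller than assumed, because that target was not reached.

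The point is worth correcting because it is cheap and bears on what may be claimed about particular patient groups. It does not threaten the main comparison. The inclusion of adherence among the subgroup variables is a real but separate fault.

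**What to change.** 1. Base any statement about moderation on a moderator-by-group-by-time term in the full-sample model, fitted separately for anxiety and neuropathy, for baseline age, sex and race or ethnicity.
2. Report the moderator-by-group contrast at 8 weeks with its 95% CI. The waitlist arm starts the app after that point, so week 8 is the comparison of app with no app.
3. Show stratum-specific estimates as description only.
4. Label the set exploratory. State that with 100 per arm there is 80% power only for a difference in effects of about d = 0.79 to 0.86 (alpha .05) or 1.03 to 1.13 (alpha .005), so a non-significant interaction does not show that the effect is uniform.
5. Separately, remove adherence from the moderator set and keep it in the later adherence analysis that the Overview already foresees.

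The cost is a few model terms and some sentences of reporting, with no new data. Since data collection is complete, the results paper should say when the change was made.
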